### Biochemical analysis

Blood sample (5 ml) will be drawn by a phlebotomist into three vacutainers (lipid profile, blood glucose, and HbA1c) and transported in ice from the field site to the laboratory within 2 h. The HbA1c sample (EDTA) will be stored at 4 °C until processing (within 24 h). The other vacutainers will be centrifuged at 1310 g. Lipid profile and blood glucose estimation will be done using a Hitachi 902 analyzer. HbA1c will be tested by low-pressure liquid chromatography (Biorad Diastat analyzer; DCCT aligned). Some of the samples (5%) will be randomly re-run to ensure quality control.

### Sample size considerations

The sample size was estimated using the stepped wedge cluster randomized design package (swCRTdesign) in R software (version 4.0.2) [18]. The following information was utilized from our recent DEDICOM-II survey: thirty clusters, a mean HbA1c of 8.9%, standard deviation 4.3, and an intra-cluster correlation of 0.09. Assuming an alpha error of 0.05 and a power of 0.9, it was estimated that a five-step design, using 12 subjects per cluster and with 6 clusters per sequence (2 from each stratum; a total of 360 subjects) will be required to detect a significant mean difference of 1% (~ 10 mmol/mol) in HbA1c level. The study would also be adequately powered (0.8) for comparisons between socio-economic classes with the same consideration using 2 clusters per step per strata.

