### Duration of treatment and follow-up

After the completion of the intervention, the subjects will be retested for the same parameters (including blood tests) every 3 months till the trial endpoint (18 months for cluster group 1). In the follow-up period, ad hoc query resolution and monthly support group/revision rounds will be conducted by the CL in the cluster till the end of the trial. Each participant will be called by telephone for each session to encourage attendance. All participants will undergo quarterly blood sampling, preventive examination compliance, and drug compliance monitoring every quarter by the research team in coordination with the CL. All participants will be provided with a symptom diary to document the medical issues faced by them through the study period and the direct and indirect costs incurred on diabetes care through the study period. All the participants will be recommended to continue the routine diabetes care, including medicines and doctor visits with their existing care provider and/or preventive checks, and will be assessed for quality of life using the pre-validated QOLID tool at baseline and last follow-up [17]. Cost of care data for both groups will be documented using the cost logs to allow for cost-effectiveness calculations. Any noted new morbidity will be referred to the primary care provider, and the intervention advice will be modified in accordance with the medical advice, even if unblinding is required. Data collection from all participants will proceed as planned irrespective of compliance or shift in residence (by virtual means if required). If consent is withdrawn during follow-up, existing data available with the team till the date of withdrawal will be used as available.

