### Quantitative data

Change in HbA1c before and after the intervention will be evaluated, accounting for SW-CRT design using the swCRTdesign package for R version 4.0.2 and the swSummary function [18]. The sustainability of the effects will be evaluated using the change in quarterly parameters after the intervention is completed. Differences between socio-economic strata will be compared as sub-group analyses depending on the income category of the clusters. Missing data will not be imputed.

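### The stated 0.9 power is that of a repeated cross-section with 12 new people per cluster each quarter, not of the closed cohort that this trial follows

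*Protocol article*

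**What the plan says.** The section on sample size considerations lists its inputs as "thirty clusters, a mean HbA1c of 8.9%, standard deviation 4.3, and an intra-cluster correlation of 0.09". The type I error is set at 0.05 and the power at 0.9. The section arrives at "a five-step design, using 12 subjects per cluster and with 6 clusters per sequence", which makes 360 people in all, as the size needed "to detect a significant mean difference of 1" percentage point in HbA1c. It adds that the study is "adequately powered (0.8) for comparisons between socio-economic classes with the same consideration using 2 clusters per step per strata". The only correlation given is the intra-cluster 0.09.

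The rest of the protocol describes one fixed group of people. The Phase 3 section recruits about 12 re-consenting survey participants per cluster. The eligibility section has them assessed at baseline and quarterly in all groups. The follow-up section says that after the intervention "the subjects will be retested for the same parameters (including blood tests) every 3 months till the trial endpoint". No section brings in new people each quarter.

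On analysis, the quantitative data section says: "Change in HbA1c before and after the intervention will be evaluated, accounting for SW-CRT design using the swCRTdesign package". It names a package and a summary function and fixes no variance model.

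**The concern.** When the same people are measured repeatedly, part of the variation between them is stable and cancels from a before-and-after comparison within the cluster. A calculation with fresh people each quarter counts that part as noise at every visit. Separately, a single intra-cluster correlation assumes that two people in a cluster are as alike across quarters as within one quarter. If the cluster effect drifts over time, precision is lost. A closed-cohort calculation needs both quantities, and the sample size section shows neither.

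At stake is whether the published power and detectable difference describe the trial being run. If the analysis followed the same model as the power calculation, the standard error of the primary HbA1c effect would be at stake too.

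**Working it through.** **Inputs from the sample size section.** 30 clusters, 12 people each, 5 sequences of 6 clusters, SD 4.3 (variance 18.49), ICC 0.09, effect 1 point, alpha 0.05 (taken as two-sided). A five-step layout has 6 periods.

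**Assumed, because the documents do not give them.** Within-person correlation r (the share of non-cluster variance that is stable within a person): 0.3, 0.5, 0.7. Cluster autocorrelation c: 1 matches the single ICC; 0.5 and 0.8 are used as sensitivity values.

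**Formula.** Weighted least squares with fixed period effects (Hussey-Hughes):

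Var = I·s²(s² + T·t²) / [(IU − W)s² + (U² + ITU − TW − IV)t²]

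Here s² is the period-specific and t² the constant part of the variance of a cluster-period mean. For I = 30 and T = 6, U = 90, W = 1980 and V = 330, so IU − W = 720 and the second bracket is 2520. Power = Φ(1/SE − 1.96).

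**1. Reproducing the stated 0.9 with 12 new people per cluster-quarter.**
- s² = 0.91 × 18.49 / 12 = 1.402; t² = 0.09 × 18.49 = 1.664.
- Var = 30 × 1.402 × (1.402 + 6 × 1.664) / (720 × 1.402 + 2520 × 1.664) = 0.0921, so SE = 0.303 and power = 0.909.
- Seven quarters (group 1 has 3 + 18 months) give 0.927. Reading 4.3 as the residual SD gives 0.882 with six periods and 0.903 with seven.

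**2. Closed cohort.** The person part moves from s² to t²:
- s² = (1 − c) × 1.664 + 1.402 × (1 − r)
- t² = c × 1.664 + 1.402 × r

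| c | r | s² | t² | SE | Power for 1 point |
|---|---|---|---|---|---|
| 1 | 0.3 | 0.982 | 2.085 | 0.258 | 0.972 |
| 1 | 0.5 | 0.701 | 2.365 | 0.220 | 0.995 |
| 1 | 0.7 | 0.421 | 2.646 | 0.172 | >0.999 |
| 0.5 | 0.3 | 1.814 | 1.253 | 0.337 | 0.843 |
| 0.5 | 0.5 | 1.533 | 1.533 | 0.315 | 0.887 |

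With c = 1, the difference detectable with 90% power, (1.96 + 1.28) × SE, is 0.84, 0.71 and 0.56 points at the three values of r, against 0.98 on the fresh-sample footing.

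**3. Strata.** One stratum has 2 of the 6 clusters per step, so its SE is √3 times the overall SE.
- Fresh samples: 0.303 × 1.732 = 0.525, power 0.477 (0.505 with seven periods). The stated 0.8 does not come out.
- For a 1-point difference between two strata, power is 0.27 to 0.29.
- Overall power of exactly 0.9 implies about 0.46 per stratum. Conversely, with c = 1 and six periods, 0.8 per stratum needs r of about 0.56, where overall power is 0.998. The two stated figures cannot come from one set of inputs.

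**4. If the analysis had a cluster effect only.** Reported SE divided by true SE, six periods:
- c = 1: 1.17, 1.35 and 1.68 at r = 0.3, 0.5 and 0.7 (intervals too wide).
- c = 0.5: 0.90 and 0.96 at r = 0.3 and 0.5 (intervals too narrow).
- The ratio crosses 1 at r = 0.24 when c = 0.8, and at r = 0.59 when c = 0.5.

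**5. If a participant effect were added but the cluster effect kept constant.** At r = 0.5 the ratio is 0.91, 0.84 and 0.72 for c = 0.9, 0.8 and 0.5. Two-sided type I error is then about 0.07, 0.10 and 0.16.

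**The case against.** The strongest reply is that the error, if there is one, is harmless. With the single constant ICC that the protocol states, true power exceeds 0.9, type I error is not inflated, and the surplus offers some cover for attrition (with 10 people per cluster, the fresh-sample power is 0.858). This stands for the overall test, but only if the cluster effect is constant over the trial, and nothing in the protocol supports that.

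A second reply is that the match to 0.9 depends on conventions: six periods and 4.3 as the total SD. That is fair. The variants still lie between 0.88 and 0.93, all on the fresh-sample footing. A closed cohort can also land near 0.9 (0.887 at c = 0.5, r = 0.5), but only with two inputs that the section does not list.

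A reader might infer that the trial will report confidence intervals that are too wide. The documents do not support this. The quantitative data section fixes no variance model and nowhere treats repeated values as independent. Its reference to change before and after the intervention could mean within-person change, which already removes stable differences between people. Random effects are commonly left to an analysis plan, and none is shown. Even for a cluster-only analysis, the direction depends on both unstated correlations.

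A reader might also infer that fresh sampling explains both stated powers. It explains only the 0.9. The 0.8 for strata is too high on that footing and is a separate fault.

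**Conclusion.** The point holds for the stated 0.9. With the listed inputs it is the power of a repeated cross-section (0.909 with six periods and 4.3 as total SD), while the trial follows a closed cohort. Its true value could be above or below 0.9: from 0.972 to above 0.999 with a constant cluster effect and r from 0.3 to 0.7, but 0.843 to 0.887 with c = 0.5 and r of 0.3 to 0.5. These ranges rest on assumed correlations. The 0.8 for strata needs recomputing on the same model, because the footing that yields 0.9 gives about half power there. What follows for the analysis is conditional: a cluster-only model would misstate the standard error, in a direction that cannot be fixed from the documents. This does not show that the sample is too small for the overall comparison. It shows that the published figures do not settle the question.

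**What to change.** In the sample size section, restate both powers from a closed-cohort stepped-wedge model. State the number of periods and whether 4.3 is the total SD, and show power over stated ranges of within-person correlation and cluster autocorrelation. Control-period data, examined blind to sequence, can narrow these ranges.

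In the quantitative data section, specify the primary HbA1c model as a mixed model with fixed calendar-quarter effects and random effects for cluster, cluster-by-period and participant, with small-sample or robust standard errors for 30 clusters. The cluster-by-period term should not be dropped: step 5 of the working shows that a participant effect beside a constant cluster effect gives intervals that are too narrow when cluster correlation decays.

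The cost is a recalculation and extra model terms, with no new data or patients. The restated power may be less favourable than 0.9 if cluster correlation decays, and the 0.8 for strata may have to be withdrawn.

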### Secondary objectives

To evaluate the effectiveness of DSME implemented using EK-DIN through a local community leader group teaching format in reducing cardiovascular risk among known diabetes patients.To compare the effectiveness of EK-DIN in improving the quality of diabetes care between socio-economic categories.To evaluate the cost-effectiveness of the EK-DIN kit when implemented through a community leader format.To assess the quality-of-life impact of a culturally embedded and locally developed novel self-management education module (EK-DIN).

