**Fig. 3 Fig3:**
[figure not shown]
Trial rollout sequence

As presented in Fig. 3, at Step 0, each cluster group starts as a control condition, with the first cluster group initiating the preparation phase and contributing control data. In Step 1, cluster group 1 enters the intervention period. Three months later, another cluster group (6 clusters) enters the intervention period. This process continues until all clusters enter the intervention. Hence, the stepped-wedge trial design involves 3 months of data in pre-intervention and 18 months in post-intervention conditions for cluster group 1, followed by 6 months in pre-intervention and 15 months in post-intervention conditions in cluster group 2, and so on. All 30 clusters will be completed in 5 steps. The study design has been specifically chosen due to the documented inherent sample size, ethical, logistical, and naturalistic advantages of a wedge cluster rollout [16] and to evaluate the baseline status, impact of intervention, and sustainability of any benefits achieved.

For each cluster group, participants of the DEDICOM-II survey will be invited for recruitment by the research team in accordance with the following selection criteria.

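### The stated 0.8 power for comparing socio-economic classes does not follow from the inputs that give the overall 0.9; those inputs give about 0.27 to 0.68 for a 1-point difference between classes, depending on the model and the number of periods

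*Protocol article*

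**What the plan says.** Under Sample size considerations, the protocol article takes from the earlier survey "thirty clusters, a mean HbA1c of 8.9%, standard deviation 4.3, and an intra-cluster correlation of 0.09". The error rates come next, "Assuming an alpha error of 0.05 and a power of 0.9", and lead to a five-step design with 12 subjects in each of 30 clusters, 6 clusters per sequence and 2 of those from each stratum, in order to "detect a significant mean difference of 1% (~ 10 mmol/mol) in HbA1c level".

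The next sentence carries the calculation over to the classes: "The study would also be adequately powered (0.8) for comparisons between socio-economic classes with the same consideration using 2 clusters per step per strata". It gives no other effect size, variance or model. As written, it is the same calculation with 2 clusters per step in place of 6.

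The comparison is a stated aim. Secondary objectives includes: "To compare the effectiveness of EK-DIN in improving the quality of diabetes care between socio-economic categories". Under Quantitative data the plan is: "Differences between socio-economic strata will be compared as sub-group analyses depending on the income category of the clusters".

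**The concern.** Each stratum holds 10 of the 30 clusters, laid out over the same five sequences. A third of the data cannot give nearly the same power for the same 1-point effect, and a contrast of two such estimates is less precise still. The two power figures stand next to each other on one set of inputs, so they should be reproducible together.

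What is at stake is how a secondary objective is read. A reader who trusts 0.8 will give a non-significant class difference more weight than the design can bear. The Discussion adds to this by citing the study's high power when it argues that positive or negative results should apply widely.

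**Working it through.** **Inputs.** From Sample size considerations: SD 4.3, ICC 0.09, 12 per cluster, 6 clusters per sequence (2 per stratum), alpha 0.05, difference 1 point. From the text with Fig. 3: "All 30 clusters will be completed in 5 steps", so 6 periods counting the all-control one. The same text gives cluster group 1 3 months before and 18 months after the start of intervention, which is 21 months, or 8 quarterly measurement times if all are used.

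**Assumptions of mine.** Two-sided test (sidedness is not stated); each quarter's 12 measurements treated as independent people; the same SD and ICC in every stratum.

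**Model.** Hussey-Hughes: fixed period effects, random cluster effect, cluster-period means.
- Between-cluster variance: τ² = 0.09 × 4.3² = 1.664.
- Residual variance: 0.91 × 4.3² = 16.83, so a cell mean has s² = 16.83/12 = 1.402.
- Var = I·s²(s² + Tτ²) / [(IU − W)s² + (U² + ITU − TW − IV)τ²]. I is the number of clusters and T the number of periods. U is the count of treated cluster-periods, W the sum of squared period totals, V the sum of squared cluster totals.
- Power = Φ(1/SE − 1.96).

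**Step 1: reproduce the overall figure.** I = 30, T = 6, U = 90, W = 1980, V = 330.
- Var = 30 × 1.402 × 11.387 / (720 × 1.402 + 2520 × 1.664) = 0.0921; SE 0.303.
- Power = Φ(3.296 − 1.96) = **0.909**. The stated 0.9 is reproduced, so the inputs are being read correctly.

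**Step 2: one stratum alone, 2 clusters per step.** I = 10, U = 30, W = 220, V = 110.
- Var = 10 × 1.402 × 11.387 / (80 × 1.402 + 280 × 1.664) = 0.276, three times Step 1; SE 0.526.
- Power = Φ(1.903 − 1.96) = **0.48**.

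**Step 3: difference between two strata, analysed separately.**
- Var = 2 × 0.276 = 0.552, six times Step 1; SE 0.743.
- Power = Φ(1.346 − 1.96) = **0.27**.
- Detectable at 0.8 power: (1.96 + 0.8416) × 0.743 = 2.1 points.

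**Step 4: one pooled model.** Stratum main effects, intervention-by-stratum terms and period effects common to all strata, fitted by generalised least squares on the same inputs. At 6 periods the SE is 0.412 within a stratum and 0.482 between two strata.

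| Quantity (1-point effect unless stated) | 6 periods | 8 periods |
|---|---|---|
| Overall power | 0.909 | 0.94 |
| Separate strata: within one stratum | 0.48 | 0.53 |
| Separate strata: between two strata | 0.27 | 0.30 |
| Pooled model: within one stratum | 0.68 | 0.77 |
| Pooled model: between two strata | 0.55 | 0.68 |
| Detectable between strata at 0.8 power, separate | 2.1 points | 2.0 points |
| Detectable between strata at 0.8 power, pooled | 1.35 points | just under 1.16 points |

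**Step 5: scaling check for separate strata.** This needs only the threefold and sixfold variance ratios.
- From exactly 0.9 overall: (1.96 + 1.2816)/√3 − 1.96 = −0.09, power 0.46; (1.96 + 1.2816)/√6 − 1.96 = −0.64, power 0.26.
- In reverse, 0.8 within a stratum implies Φ(2.8016 × √3 − 1.96) = 0.998 overall.

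**Step 6: other assumptions.** A one-sided test at 6 periods with separate strata gives 0.60 within and 0.38 between. I also varied the number of periods, the sidedness and the cluster and individual autocorrelations. Among variants with overall power between 0.88 and 0.92, the highest values were about 0.55 within and 0.34 between for separate strata, and about 0.75 and 0.67 for the pooled model.

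**The case against.** The strongest reply is that 0.48 and 0.27 belong to one analysis, not to the trial. They require each stratum to have its own period effects and the pooled SD and ICC. A sub-group comparison could equally be run as interaction terms in one model with shared period effects, and between-strata power is then about double. That stands. A reader might infer that 0.27 is the study's true power for this objective, or that a real 1-point class difference would be missed three times in four. The documents do not fix the model, so they do not support either statement without that condition.

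The second reply is that the trial follows the same participants every quarter, so treating the measurements as independent people understates power. That also stands. The article gives no within-person correlation; as an assumption, an individual autocorrelation of 0.3 puts the pooled between-strata power at 0.69 (6 periods) to 0.82 (8 periods), and 0.5 puts it at 0.83 to 0.93. But overall power is then 0.97 or more. The nearest approach I found concerns the effect within one stratum, which is not a comparison between classes: the pooled model at 8 periods with autocorrelation 0.1 gives 0.81, with overall power 0.96. Correlation moves both figures together and does not produce 0.9 beside 0.8.

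Third, nothing in the article says that a non-significant class difference will be taken as equal benefit, and the comparisons are already called sub-group analyses. That is fair: the misreading is a risk for readers, not a stated intention. Details of the interaction model can properly sit in an analysis plan that is not shown here. The power figure, however, is stated in the article and can be judged there.

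**Conclusion.** The concern holds in this form: the 0.8 does not follow from the inputs it claims to share with the 0.9. On those inputs, power for a 1-point difference between two classes is about 0.27 to 0.30 with separate strata and 0.55 to 0.68 with a pooled common-period model. For a 1-point effect within one class it is 0.48 to 0.53 and 0.68 to 0.77 respectively. These ranges rest on a two-sided 0.05 test, equal SD and ICC across strata, 6 to 8 periods and no within-person correlation.

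A reader might go further and infer that no assumption could yield 0.8 by class, or that the trial as a whole is underpowered. Neither is supported. Sufficient within-person correlation does reach 0.8 by class, only not with overall power near 0.9. The primary calculation reproduces, and the 360-subject sample size is untouched. The error is confined to a supporting claim for a secondary objective.

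**What to change.** In Sample size considerations, replace 0.8 with the power, or the difference detectable at 0.8 power, for a named contrast (the effect within a class or the difference between two classes) under the model that will actually be fitted. State the number of periods and any within-person correlation assumed, and use the same assumptions for the overall figure.

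If Quantitative data adopts the pooled interaction model, quote that model's figures (about 0.55 at 6 periods or 0.68 at 8 for a 1-point difference between classes) and not 0.27. If the strata will be analysed separately, quote about 0.27 or 0.30. In either case, add that a non-significant class difference will not be read as equal effect.

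The change is text only. It needs no further recruitment or data and alters nothing in the primary analysis. The price is a less favourable stated power for the class comparison.

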## Statistical analysis

### Qualitative data

Interview transcripts will be transcribed and translated into English, cross-checked against the original recording, and coded using ATLAS.ti 7.2 or NVIVO 14.0 software for thematic analysis. The research team will code the data into provisional themes in accordance with the six phases of Maguire and Brid [19]. The analysis will be iterative, moving bi-directionally through the phases. The provisional themes will be reviewed for nuances and sub-themes before defining and naming the themes. the defined themes/subthemes will then be mapped onto the factors listed in Andersen’s Behavioural Model (ABM) [20] to understand the barriers and facilitators to the proposed intervention and the Health Beliefs Model to evaluate diabetes-related perceptions of the community. Any additional themes will be recorded as new unmapped items.

